### Indications for discontinuation of vaccinations in all volunteers:

If 3 or more of the volunteers participating in this trial develop an SAE or severe AE judged as definitely, probably or possibly related to the vaccine, and clinically significant by the Principal Investigator or designee, IAVI will request a review by the DSMB and the trial will be suspended pending a review of all safety data by the DSMB. The study treatment may be unblinded at the discretion of the DSMB. Following this review, the DSMB will make a recommendation to the Principal Investigator and IAVI regarding the continuation of the trial. Unless the trial is permanently discontinued, PI, the research team, and IAVI will not be made aware of any unblinded results.

15. **Procedures to Minimize Risks**: All study procedures will be performed by [name]. and his designees. All vaccinations with electroporation will be performed only by individuals who have successfully completed Ichor’s formal training seminar. The seminar will be conducted by Ichor personnel and will require approximately 60-90 minutes to complete. Topics will include setup and operation of the equipment, procedures for administration of the DNA vaccine, troubleshooting, and device care and storage. Each participant must successfully complete at least three mock administration procedures in order to demonstrate competency.

No more than one volunteer per day will be enrolled for the first four volunteers to receive electroporation in each dose group. For these four volunteers, an additional telephone call to assess safety and adverse events will be made on the day following vaccination. If four vaccinations by electroporation have occurred without greater than moderate adverse events, the remainder of the group can be enrolled with no fixed interval between volunteers.

All intramuscular vaccinations will be given by skilled nursing staff or physicians using sterile technique. The phlebotomy procedures will be performed by skilled professionals using sterile technique. The site of each vaccination will be given in alternating upper arms. No more than 550 mL of blood will be taken from an individual over an 8-week period. If a female subject becomes pregnant during the course of the study she will be followed up through to the end of the pregnancy (either birth of the baby or termination of the pregnancy). If the pregnancy results in birth, a pediatrician will examine the baby approximately 2-4 weeks after birth.

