## Sample Size and Power Calculations

A minimum of 40 volunteers will be enrolled in the study; 32 volunteers will be given active vaccines (24 EP and 8 IM) and 8 volunteers will be given placebo via EP route. An over-enrolment of about 10% (4 volunteers) will be permitted. This small sample size is appropriate for an exploratory dose-escalation study of a novel product while safety and immunogenicity of the vaccine are investigated.

The rate of Serious Adverse Events related to vaccine will be used as one measure of the safety of the candidate vaccine. Adverse Events that may be temporarily incapacitating (for example, loss or cancellation of work or social activities), which could make a vaccine impractical for large scale use if they occur in more than a small proportion of cases, will also be assessed.

One method of assessing the sample size is to consider the precision for estimation of incidence of serious adverse events.

*Prior to the enrollment of the medium dose level group:*

If none of the volunteers receiving the vaccine experiences an SAE related to vaccine (n=8), the 95% upper confidence bound for the rate of these adverse events in the population is 0.37 by Clopper Pearson method.

*Prior to the enrollment of the highest dose level group:*

If none of the volunteers receiving the vaccine experiences an SAE related to vaccine (n=16), the 95% upper confidence bound for the rate of these adverse events in the population is 0.21.

*After all volunteers have received the initial dose:*

If none of the volunteers receiving the vaccine experiences an SAE related to vaccine (n=24), the 95% upper confidence bound for the rate of these adverse events in the population is 0.14.

There is very limited power for comparison of event rates between treatment arms.

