***Safety and Tolerability:***

All adverse events will be reported, grouped as to whether or not they qualify as SAEs, their severity grading, and their relationship to vaccine (as judged by the investigator and reviewed by the Safety Review Board).

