1. **Risk:** This project entails **moderate risk** to subjects. Monitoring will be conducted a) by the Principal Investigator (PI) in consultation with the Clinical Research Officer of the Clinical Translation Science Advisory Committee and b) by the PI and the Rockefeller University Institutional Review Board (IRB), through annual reports of progress and by immediate notification of adverse events by the PI to the IRB, the ACCTS, and any federal regulatory agency (e.g. FDA) when appropriate or required.

2. **Determine the need for a DSMB:** This study is a Phase I study which exposes the subjects to “moderate risk” as the ADVAX vaccine is an experimental vaccine that will be administered using an experimental delivery device TriGrid that has never been administered to healthy volunteers before. A Data and Safety Monitoring Board (DSMB) will be established for this study. See details about the DSMB below.

3. **Safety Review Plan:** Subjects will have regularly scheduled visits to the outpatient clinic. Please see Appendix A “Schedule of Procedures” for the details of these visits. Safety laboratory testing (hematology, clinical chemistries, pregnancy testing, hepatitis B/C profiles, RPR/TPHA testing, anti-DS-DNA antibody test, and urinalysis) will be performed at the Memorial Sloan Kettering Cancer Center (MSKCC). The results of these tests will be reviewed, evaluated, signed and dated by the Principal Investigator or his designee in real time (for routine labs and CD4/8 cell counts, 24 to 48 hours from the time of the lab analysis). The results of the HIV antibody tests at the initial screening, performed by the New York State Department of Health AIDS Institute (NYS DOH AI), will be available for review and evaluation from 72 to 120 hours after lab analysis dependent upon the test result. After the trial has commenced, on all subsequent HIV antibody tests where the results are positive, the NYS DOH AI will also perform an HIV-RNA test on that sample. Other specialized virological and immunological testing will be performed either in real time or “batched” and analyzed at a later date. Abnormal laboratory results will be reviewed and discussed by the clinical team on a regular basis at the weekly clinical meeting at ADARC and minutes of those discussions will be kept. A copy of routine laboratory results from CLEP certified laboratories will be provided to each subject during their outpatient visits.

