No more than one volunteer per day will be enrolled for the first four volunteers to receive electroporation in each dose group. For these four volunteers, an additional telephone call to assess safety and adverse events will be made on the day following vaccination. If four vaccinations by electroporation have occurred without greater than moderate adverse events, the remainder of the group can be enrolled with no fixed interval between volunteers.

A. **Description of Adverse Events (AE) Detection and Reporting:**

**i. Adverse Event Definition**: An adverse event is any noxious, pathologic, or unintended change in anatomical, physiologic, or metabolic functions, as indicated by physical signs, symptoms, and/or laboratory changes occurring in any phase of the clinical trial, whether associated with drug and whether or not considered drug related. All of the following are to be considered adverse events:

- An exacerbation of a pre-existing condition.
- An inter-current illness.
- Any drug interaction.
- Any event related to a concomitant medication.
- Development of an abnormal laboratory value or a significant change from baseline in a laboratory value within the range of normal, considered by the investigator to be clinically important.

Any adverse event prior to the first vaccination will be reported as a pre-existing condition on the “previous conditions” source document. At each outpatient visit, subjects will be questioned and/or examined by the PI or his designee for evidence of AEs. The onset and end dates, severity and relationship to study vaccine and EP device will be recorded in the medical record for each event.

**ii. Assessment of Severity:** The severity of the AE will be assessed according to the Adverse Event Severity Assessment Table (see Appendix C).

**iii. Serious Adverse Event (SAE) Definition:** An SAE is an AE that results in any of the following outcomes.

- Death
- Life threatening condition
- Hospitalization or prolongation of stay
- Persistent or significant disability or incapacity
- Congenital anomaly or birth defect
- Medically significant event, including laboratory abnormalities

Important medical events that do not result in death, are life threatening, or require hospitalization, may be considered SAEs when, based on appropriate medical judgment, they may jeopardize the volunteer, or may require medical/surgical intervention to prevent one of the outcomes listed in this definition.

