**A Data and Safety Monitoring Board has been composed to oversee data and safety for the Rockefeller/ADARC site.**

## Standard Operating Procedures (SOPs) for the Data and Safety Monitoring Board (DSMB):

- The charter of the DSMB is to provide an ongoing assessment of volunteer safety during the ADVAX + EP Clinical Trial. The DSMB will consist of independent individuals who have no relationship to the Principal Investigator and Co-Investigators involved in the trial. No member of the DSMB will have any direct responsibility for the clinical care of trial volunteers. No representative of IAVI, Ichor or ADARC or their designees may be a member of the DSMB. However, the DSMB may invite the principal investigator (PI) or designee and an IAVI and/or ADARC representative to an open session of a DSMB meeting to provide information on study conduct, present data, or to respond to the members’ questions.
- The names, university affiliation and title, area of expertise, and contact information of each of the DSMB members are provided to the IRB (as listed above).
- All updated versions of the protocol and Investigator Brochure (I.B.) will be provided to the DSMB members.
- The DSMB will teleconference to review the trial data at least 14 days after both of the following criteria have occurred in the first group: after 12 volunteers in the first group have received their first vaccination *and* at least 8 volunteers in the same group have received both vaccinations. Similarly for group two, the DSMB will teleconference after 14 volunteers in the second group have received their first vaccination *and* at least 8 volunteers in the same group have received both vaccinations before proceeding to the next dose group. The DSMB must approve escalation to the next dose. At least two members are required to review the data before approval. Additional meetings will take place if there are indications for an interim review, which may be unblinded at the discretion of the DSMB.
- The study team will provide the DSMB with updated records of all adverse events (AEs) of a grade 2 or higher prior to each teleconference. The DSMB will be asked to review all severe clinical adverse/reactogenicity events judged by the Principal Investigator or designee to be possibly, probably or definitely related to vaccine.

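### The suspension trigger and the DSMB's severe-event reviews depend on relationship to the vaccine alone, so severe events attributed only to the electroporation device do not count, although that attribution is recorded

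*Protocol*

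**What the plan says.** The suspension rule stands in the Protocol under Indications for discontinuation of vaccinations in all volunteers. It takes effect once at least three volunteers across the whole trial "develop an SAE or severe AE judged as definitely, probably or possibly related to the vaccine", with a further condition that the investigator finds the event clinically significant.

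The DSMB operating procedures use the same attribution. The board's named review of severe clinical and reactogenicity events is limited to those "judged by the Principal Investigator or designee to be possibly, probably or definitely related to vaccine". A parallel item covers severe laboratory events confirmed on retest, again only if vaccine-related.

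Two other places in section 14 use a wider attribution. Under Adverse Event Definition, "relationship to study vaccine and EP device will be recorded in the medical record for each event". Under Annual Reporting of AEs, the table for the review board shows attribution to the drug or to the procedure.

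The primary objective (section c) is the safety of ADVAX given by TriGrid EP. Section 14, item 2, justifies the DSMB partly by an "experimental delivery device TriGrid that has never been administered to healthy volunteers before".

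In the analysis section, under Safety and Tolerability, all adverse events are reported, grouped among other things by "their relationship to vaccine (as judged by the investigator and reviewed by the Safety Review Board"). No device grouping is named there.

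**The concern.** The protocol keeps vaccine and device as two separate attributions. Given that separation, the words 'the vaccine' in the suspension rule cannot safely be read to include the device. A severe injury that the investigator ascribes to the electrodes or the pulse, and not to the DNA, falls outside the trigger and outside both named DSMB reviews.

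The hazard is one the protocol itself expects. The risk section describes a possibly painful muscle contraction, tingling in about 10% of subjects, and a possible rise in the frequency or severity of local reactions with EP. At stake is whether the trial's one count-based suspension rule responds to harm from its new element. The more plainly the device is the cause, the less likely the event is to count.

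**Working it through.** **1. The plan's own safety figures.** The sample-size section gives upper 95% bounds of 0.37, 0.21 and 0.14 for the rate of vaccine-related SAEs when none occurs in 8, 16 or 24 volunteers. The two-sided Clopper-Pearson bound with zero events is 1 − 0.025^(1/n):

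- n = 8: 0.369
- n = 16: 0.206
- n = 24: 0.142

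All three reproduce. With zero events the bound depends on n only, so the attribution label changes none of them. The protocol states no operating characteristic for the suspension trigger.

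**2. Attribution wording side by side.**

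| Place in Protocol | Attribution used |
|---|---|
| Adverse Event Definition (recording) | vaccine and EP device, separately |
| Annual Reporting of AEs | drug or procedure |
| Suspension trigger | vaccine only |
| DSMB review, severe clinical events | vaccine only |
| DSMB review, severe laboratory events | vaccine only |
| Safety tables | all events; grouped by vaccine relationship only |

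**3. What is scheduled after the mid-dose stage.** The DSMB procedures and the randomization table set two teleconferences, one before the mid-dose stage and one before the high-dose stage. None is set for the high-dose stage (8 ADVAX/EP + 3 saline/EP = 11 EP volunteers) or for the optional third vaccination. Additional meetings are possible, but their indications are not defined. In that period the trigger is the only route to DSMB review with a defined count.

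**4. Sensitivity of the trigger to EP harm.** Inputs:

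- EP recipients: 24 ADVAX + 8 saline = 32 (sample-size section).
- Threshold: 3 volunteers (suspension rule).
- p, the proportion of EP recipients with a severe or serious event caused by the procedure: assumed.
- s, the share of those events judged at least possibly vaccine-related: assumed.

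Volunteers are taken as independent, each counted event is taken as clinically significant, and events in the 8 IM recipients are left out. Then X ~ Binomial(32, p·s), and P(X ≥ 3) = 1 − [P(0) + P(1) + P(2)].

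For p = 0.10 and s = 1: 1 − [0.9^32 + 32 × 0.1 × 0.9^31 + 496 × 0.01 × 0.9^30] = 1 − [0.034 + 0.122 + 0.210] = 0.63.

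| p | s = 1 | s = 0.5 | s = 0.25 | s = 0 |
|---|---|---|---|---|
| 5% | 0.214 | 0.045 | 0.007 | 0 |
| 10% | 0.633 | 0.214 | 0.045 | 0 |
| 15% | 0.878 | 0.434 | 0.117 | 0 |
| 20% | 0.968 | 0.633 | 0.214 | 0 |

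The expected number of volunteers affected is 32 × 0.10 = 3.2 at 10% and 32 × 0.15 = 4.8 at 15%. Within each row only the attribution share changes.

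**The case against.** The strongest reply is that several safeguards carry no attribution condition.

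- The DSMB receives records of all adverse events of grade 2 or higher before each teleconference, and it must approve each escalation.
- The rule for the first four EP recipients in each dose group looks at any event above moderate. Over 4 × 3 = 12 such volunteers, the chance of at least one severe event is 1 − 0.9^12 = 0.72 at a 10% rate.
- Volunteers with injection reactions of Grade 3 or above are removed.
- Serious events go to the review board within two working days.

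This stands as far as it goes, so a reader should not infer that the DSMB never sees device harm. But the grade 2 records are tied to teleconferences, and none is scheduled after the high-dose stage opens. The first-four rule governs the pace of enrolment only. The removal rule acts on one person and only for injection reactions. The serious-event reports go to the review board, not to the DSMB. None of these does the work of a trial-wide count.

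A second reply is that the trigger rests on what is judged possibly related. ADVAX/EP and saline/EP recipients undergo the same procedure, so an investigator unaware of assignment could judge a saline/EP reaction possibly vaccine-related, and it would count. That is right. A reader might infer that events in the saline/EP group can never count, and the text does not support that. For the same reason the s = 0 column is an extreme case, and setting 0.88 against 0 as the likely effect would mislead.

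A third reply is that recording two attributions does not oblige the protocol to use both. That is also fair. But nowhere does it say that device-attributed events are left out deliberately, or why.

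**Conclusion.** The point holds for the suspension trigger and for the DSMB's two named severe-event reviews. All three depend on vaccine relationship, while the protocol records device relationship separately and reports procedure attribution annually. Severe events attributed only to the device would not count toward suspension. The gap matters most in the high-dose stage and after the optional Week 36 vaccination.

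The size depends on two quantities the protocol does not give. At an assumed 10% severe EP-event rate, the chance that the trigger is met is 0.63, 0.21 or 0 as all, half or none of the events are judged vaccine-related. At 15% it is 0.88, 0.43 or 0.

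Two wider readings are not supported. A reader might infer that the safety tables leave out device harm. They report all adverse events, relatedness is only a grouping there, and the primary endpoints (section d) carry no attribution condition. A reader might also infer that the precision statement is wrong. Its bounds are correct and need no change; vaccine-related SAEs are only one of the safety measures named there.

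**What to change.** Reconcile the attribution wording of the suspension rule and of the two DSMB severe-event review items with the Adverse Event Definition and Annual Reporting paragraphs. The protocol should then state explicitly how events attributed to the EP device or procedure are treated in each of the three. As a consistency edit, show the recorded device attribution beside the vaccine attribution in the Safety and Tolerability grouping.

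No threshold or clinical rule is proposed here; what the reconciled rule says is for the sponsor to decide.

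The cost is a wording amendment in three places plus the one table edit. No new data are needed, because the device attribution is already recorded for each event. The downside is that a reconciled trigger may be reached sooner.

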**APPENDIX A: SCHEDULE OF PROCEDURES**

| Visit Day (D)/Week (W) | Screen D – 42 | D  0 | **D3 Phone | Wk 1 | Wk 2 | Wk4 | Wk  8 | D 59  Phone | Wk 9 | Wk  10 | Wk  12 | Wk  16 | Wk  24 | Wk 36 | D 255 Phone+ | Wk 37+ | Wk 38+ | Wk  40 | Wk 44+ | | Wk  48 | | Wk  56 |
| --- | --- | --- | --- | --- | --- | --- | --- | --- | --- | --- | --- | --- | --- | --- | --- | --- | --- | --- | --- | --- | --- | --- | --- |
| Visit Windows  ( Days) |  |  | 2 | 2 | 2 | 4 | 4 | 2 | 2 | 2 | 4 | 7 | 7 | 7 | 2 | 2 | 4 | 7 | 7 | 7 | | 7 | |
| Informed Consent | **X** |  |  |  |  |  |  |  |  |  |  |  |  |  |  |  |  |  |  |  | |  | |
| ADVAX Vaccine |  | **X** |  |  |  |  | **X** |  |  |  |  |  |  | **X+** |  |  |  |  |  |  | |  | |
| Medical History | **X** | **X** |  | **X** | **X** | **X** | **X** |  | **X** | **X** | **X** | **X** | **X** | **X** |  | **X+** | **X+** | **X+** | **X+** | **X** | | **X** | |
| General Physical Exam | **X** |  |  |  |  |  |  |  |  |  |  |  |  |  |  |  |  |  |  |  | |  | |
| Directed Physical Exam |  | **X** |  |  |  | **X** | **X** |  |  |  | **X** |  | **X** | **X** |  |  | **X+** | **X+** | **X+** | **X** | | **X** | |
| Pregnancy Test (women) | **X** | **X** |  | **X** | **X** | **X** | **X** |  | **X** | **X** | **X** | **X** | **X** | **X** |  | **X+** | **X+** | **X+** | **X+** | **X** | | **X** | |
| Pregnancy Avoidance Counseling | **X** | **X** |  | **X** | **X** | **X** | **X** |  | **X** | **X** | **X** | **X** | **X** | **X** |  | **X+** | **X+** | **X+** | **X+** | **X** | | **X** | |
| Risk Reduction and Safe Sex Counseling | **X** | **X** |  | **X** | **X** | **X** | **X** |  | **X** | **X** | **X** | **X** | **X** | **X** |  | **X+** | **X+** | **X+** | **X+** | **X** | | **X** | |
| HIV Testing (ref 11.1) Pre-/Post HIV test Counseling b | **X** | **X** |  |  |  | **X** | **X** |  |  |  | **X** |  | **X** | **X** |  |  |  |  |  | **X** | | **X** | |
| Adverse Events |  | **X** | **X** | **X** | **X** | **X** | **X** | **X** | **X** | **X** | **X** | **X** | **X** | **X** | **X+** | **X+** | **X+** | **X+** | **X+** | **X** | | **X** | |
| Serious Adverse Events |  | **X** | **X** | **X** | **X** | **X** | **X** | **X** | **X** | **X** | **X** | **X** | **X** | **X** | **X+** | **X+** | **X+** | **X+** | **X+** | **X** | | **X** | |
| Vital Signs (pre and 30-45 minute post vaccination) |  | **X** |  |  |  |  | **X** |  |  |  |  |  |  | **X+** |  |  |  |  |  |  | |  | |
| Local and Systemic Reactogenicity Assessment (pre & post vaccination) |  | **X** | **X** | **X** | **X** | **X** | **X** | **X** | **X** | **X** | **X** |  |  | **X+** | **X+** | **X+** | **X+** | **X+** | **+** | **+** | |  | |
| Hep Bs Ag, Hep C ABS, Syphilis | **X** |  |  |  |  |  |  |  |  |  |  |  |  |  |  |  |  |  |  |  | |  | |
| Hematology and Clinical Chemistry | **X** | **X** |  |  | **X** | **X** | **X** |  |  | **X** | **X** | **X** | **X** | **X** |  |  | **X+** | **X+** |  | **X** | | **X** | |
| Anti-DS DNA |  | **X** |  |  |  |  |  |  |  |  |  | **X** |  |  |  |  |  | **X** |  | **X** | |  | |
| Urine dipstick | **X** | **X** |  |  | **X** | **X** | **X** |  |  | **X** | **X** | **X** | **X** | **X** |  |  | **X+** | **X+** | **X+** | **X** | | **X** | |
| Immunology (CD4/CD8) |  | **X** |  |  |  |  |  |  |  |  |  |  | **X** |  |  |  |  |  |  |  | | **X** | |
| PBMCs for Cellular immunogenicity assays (ELISPOT&CFC) and storage |  | **X** |  | **X** | **X** | **X** | **X** |  | **X** | **X** | **X** | **X** | **X** | **X** |  | **X+** | **X+** | **X+** | **X+** | **X** | | **X** | |
| Binding/ Neutralizing Antibody Responses |  | **X** |  | **X** | **X** | **X** | **X** |  | **X** | **X** | **X** | **X** | **X** | **X** |  | **X+** | **X+** | **X+** | **X+** | **X** | | **X** | |

ET = Early Termination

b Post-test counseling will be offered after HIV test results are available, at the next study visit or when available according to the site’s SOPs

** The first four subjects in each dose group who receive their vaccination by electroporation, an additional telephone call to assess safety and adverse events will be made on the day following the vaccination

**+**Vaccination on Week 36 and follow-up visits on Weeks 37, 38, 40 and 44 are optional, and apply only to those volunteers randomized to EP in the high dose cohort who elect to receive a third vaccination

